### Study preparation (protocols and drugs)

**Study protocol revision:** The study will undergo necessary protocol revision based on the clinical trial data obtained. The revised study protocol must be approved by the sponsor, investigator, and ethics committee.

**Production and storage of drugs:** Investigational drugs and control drugs should meet the requirements of GCP, be produced under conditions that meet the requirements of GMP, and must have drug inspection reports.

**Preparation of label:** The study drug will be packaged in a pre-labeled cartridge for use by subjects. The label will also be attached to the smallest package of the drug when it leaves the factory. The name of the drug, drug number, specification, usage, storage, expiration date and manufacturer are listed on the label of each cartridge, and the label is marked "for clinical research only".

**Drug number:** Drug number in the form of T#\*\*\* or Z#\*\*\*, where T stands for experimental drug and Z stands for control drug; # is X or Y, where X represents test 1 and Y represents test 2; \*\*\* is a 3-digit serial number, starting from 001 to the desired number. Drug delivery, distribution and inventory: The investigational drug shall be transported to the study center in accordance with the standard operating procedures of Xi 'an Libon Pharmaceutical Co., LTD. Experimental drugs will be stored according to label instructions. The investigator shall be responsible for dispensing and inventorying test drugs. The investigational drug is to be used only on the subject of the clinical trial, and the dosage and usage of the investigational drug shall be in accordance with the protocol, and the remaining intact investigational drug package shall be returned to the sponsor and shall not be

transferred to any non-clinical trial participant.

**Administration plan and study period:** This product is given subcutaneously in a single dose, the injection site is abdomen subcutaneously. This product cannot be injected intravenously or intramuscularly. On the day of administration, the corresponding dose of the test drug was injected subcutaneously through the abdomen in a single multi-point injection according to the dose cohort to which the subject belonged.

### Research procedures

**Screening:** The benefits and risks of the trial should be explained in detail to the subjects. Prior to screening evaluation, subjects should be informed and sign informed consent. After signing the informed consent, each subject will undergo screening examination and can be enrolled after meeting the inclusion criteria through various examinations.

**Enrollment:** Subjects who meet the screening criteria for enrollment will be enrolled in this study.

### Randomization

① **Optimal single point subcutaneous dose test of long-acting ropivacaine injection (study 1)** : Six areas were selected in the abdomen of the subject abdominal injection site, starting from the xiphoid region, marked clockwise as I, II, III, IV, V and VI, and the first administration area was randomly determined, the first injection site was marked in the first administration area, and the drug was marked clockwise (the dose increased from small to large). The last area after randomization was the blank control area.

② **Safety, tolerability and pharmacokinetics of long-acting ropivacaine injection in a single subcutaneous administration of different doses in healthy subjects (study2)** : Each subject, according to the abdomen four partition method (that is, through the umbilicus in vertical and horizontal stroke, the two lines intersect the abdomen is divided into four area) with four areas, from the xiphoid process position clockwise ordinal annotation for I, II, III, IV, random initial dosing area is determined, and in turn clockwise in round 1, 2, 3, round 4 final area as blank control area.

Upon signing the informed consent, subjects will be assigned a S+ 3-digit subject screening number, ascending from 001; Eligible subjects in each dose cohort will be assigned a 4-digit subject number upon enrollment. Subject number assignment information for each dose cohort is shown in the following table 4:

**Table 4 Subject Numbering table**

| Queue | Subject Number | dosage (mg) |
|-------|----------------|-------------|
| A     | 1001~1009      | 150         |
| B     | 2001~2008      | 230         |
| C     | 3001~3008      | 300         |
| D     | 4001~4008      | 350         |
| E     | 5001~5008      | 400         |

Subject numbers for each dose group will be assigned from the smallest to the largest in accordance with the order of enrollment of the subject. Subject numbers will not be omitted. Cohort A 150mg group was randomly divided into experimental group and control group, and then divided into 3 batches for the test, with 1 case in the first group and 1 case in the positive control group. In the second group, there were 2 cases in experimental group and 1 case in positive control group. In the third group, there were 3 cases in experimental group and 1 case in positive control group. The randomization statistician used SAS software to generate the randomization allocation table of

subjects in Cohort 1001-1009 in batches, according to which drugs were given to the experimental group and control group.

**Note :** (1) the random grouping of cohort A should follow the blind design, and the subjects should not know their own group; (2) The drug administration researcher and the pain measurement researcher should not be the same person.

**Administration:** After the subjects were admitted to the clinical trial ward, they were examined for vital signs (including armpit temperature, pulse, decubital blood pressure, etc.) in the morning of the next day (the day of administration) before subcutaneous administration.

**Optimal single point subcutaneous dose test of long-acting ropivacaine injection (study 1) :** 0.6mL (12mg), 0.8mL (16mg), 1.0mL (20mg), 1.2mL (24mg) and 1.5mL (30mg) were subcutaneously injected according to points 1, 2, 3, 4 and 5 marked on the abdomen of the subjects respectively.

**Safety, tolerability and pharmacokinetic of a single subcutaneous dose of long-acting ropivacaine injection in healthy subjects (Experiment 2):** Each subject in the same cohort was assigned four areas according to the abdominal area of laparoscopic surgery, and the initial drug administration area was randomly determined according to the four-region abdominal method. Injection sites were marked, and subcutaneous injection was performed successively according to the serial number of injection sites. According to the designed dosing dose for each cohort, the dosing points were evenly distributed on the circumference of circles 1,2 and 3 with diameters of 40mm, and the dose was administered each time until the total dose designed for each cohort was reached. If the number of dosing points is not evenly distributed on three circles, one dosing point is reduced or added on the third circle, but the dosing points in the third circle are still evenly distributed (i.e., the dosing dose is evenly distributed on the circle).

**Adverse events (including SAE) :** In the event of any perceived symptoms, new or worsening symptoms, subjects should be immediately given appropriate medical assistance. The relevant adverse events shall be handled by referring to the section of "Possible adverse events and rescue measures" in this plan. If they meet the definition, they shall be reported as adverse events or SAE reports. Record the most severe level of adverse events during the trial. All pregnancies detected after administration and their outcomes (spontaneous abortion, selective termination of pregnancy, ectopic pregnancy, normal delivery or congenital malformations, etc.) should be reported in writing. Male subjects should report the pregnancy of their spouse after dosing. Pregnancy itself is not reported as an adverse event. If the pregnancy course/outcome meets SAE criteria, the investigator should report it according to SAE reporting procedures. Pregnancy outcomes should be followed up and recorded even if subjects drop out of the study.

Local skin irritation reaction at the injection site: score local skin irritation reaction at the injection site according to the skin irritation reaction evaluation scale.

Upon withdrawal from the study, the subjects will undergo further examination if there are new or increased outliers from laboratory tests. Results should be recorded in the case report form or in the corresponding section of the eCRF.

All adverse events and SAE present at the time of study termination should be followed up to their baseline remission level or be stable or lost to follow-up, unless, in the opinion of the investigator, remission is not likely due to the subject's own disease. For these cases, the investigator should record them on the medical record.

## **Drug combination**

**Drugs not permitted during the study:** Any drug is prohibited from the screening period until the completion of the final clinical observation and laboratory examination. Including any prescription drugs, over-the-counter drugs, chinese herbal medicine, special medical use formula food, health care products.

**Drugs allowed during the study:** In case of emergency, consideration with the safety and health of the subjects, if it is necessary to use other drugs according to the judgment of the researcher, the drugs can be used under the guidance of the researcher, and the sponsor shall be informed of the drug use in a timely manner. All drug combinations and treatments must be recorded on the case report form or at the corresponding location on the eCRF. Include the name of the product (chemical and trade name), dosage, method of administration, purpose, and start and end dates.

### **Blinded design**

**Principles of blinded design:** Because the packaging and properties of the test drug and the control drug in this study were different, it was impossible to blind the researchers. Therefore, the blind method was adopted in this study to ensure that the subjects did not know which drug they received, so as to avoid the bias caused by the subjective factors of the subjects on the efficacy. The randomized grouping of cohort A in trial 2 of this study should follow the blind design. Subjects should not know their grouping, and the drug administration researcher and pain measurement researcher should not be the same person.

**Blind storage:** In cohort A of trial 2 of this study, the order of each subject receiving test preparations or control preparations will be determined by a random table, which randomly generated by statistical units using SAS(9.4 or higher version) in 1:1 block groups. The selected block length and random seed number are sealed in the blind as confidential data.

**Blind emergency letters:** At the same time as the drug was blindfolded, clinical trial research centers should be provided with emergency letters. In case of emergency unblinding, the investigator can obtain the grouping information of the subjects according to the prompt of the emergency letter.

In the emergency letter, the contact information and address of the unit and the date should be reported immediately in case of emergency. If the emergency letter is opened, please indicate who opened it, the date opened, the reason and record it in the electronic medical record report form.

**Provisions on opening and reading emergency letters:** In the event of an emergency (such as serious adverse reaction) or the participants need to rescue must know receive what kind of processing, subject to consent by the center is a major researcher, emergency letters are opened by researchers. Once the emergency mail is opened, the subject with this number will withdraw from the study, the reason should be recorded in the medical report, and inform the bid and CRA. All emergency correspondence will be recalled at the end of the trial for blind post-trial review.

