### Study design:

A randomized, single-blind, positive-controlled, single-dose subcutaneous, dose-increasing clinical study based on the characteristics of laparoscopic surgery.

**Test drug:** Long-acting ropivacaine injection Specification: 200mg/10mL; Manufacturer: Xi 'an Libang Pharmaceutical Co., LTD. Period of validity: 24 months;

**Control drug:** Ropivacaine hydrochloride injection, specification: 100mg/10mL; Manufacturer: AstraZeneca AB; Validity: 36 months.

**Number of planned subjects:** This study plans to enroll 50 healthy subjects, with unlimited male and female ratio. Whole blood and blank plasma samples were collected from 6 healthy subjects. An exploratory trial was conducted to investigate the optimal single point subcutaneous dose of long-acting ropivacaine injection in 3 healthy subjects. The safety, tolerability, pharmacokinetics, and pharmacodynamics of long-acting ropivacaine injection in a single subcutaneous administration of different doses were investigated in 41 healthy subjects.

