The test drug (test preparation or control preparation) shall be injected subcutaneously at a position enantiograms on the circumference; Observation of local skin irritation reaction at the injection site: The evaluation of local skin irritation reaction at the injection site was evaluated according to the skin irritation scoring system, and the scores were performed before and after administration at 20min,40min,1h,2h,6h,24h 48h 72h, as shown in the skin irritation reaction rating table.

Local skin irritation reactions, including pain or tenderness at the injection site, erythema or redness at the injection site, induration at the injection site, swelling at the injection site, itching at the injection site, etc., were determined and recorded according to the evaluation criteria for Common adverse events (CTCAE) (V5.0,

published on November 27,2017).

The onset time of analgesic maintenance time and the intensity of acupuncture pain were measured.

The linear distance between two adjacent injection sites on the same circumference was measured and recorded.

The drug administration investigator and the pain measurement investigator should not be the same person;

Subjects should be hospitalized for observation for 72 h after administration before discharge

[figure not shown]

Figure 2: Schematic diagram of four abdominal regions

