## Pharmacodynamics methods:

**Experimental design, (1) Analgesic range measurement (Experiment 1) :** After the single point of administration, pain points were determined in two directions (when the VAS value of the test point (n) 1cm away from the point of administration was  $\geq 4$ , The measurement can be terminated at (n+1) time point) at 15min, 30min, 45min $\pm$ 3min, 1h, 1.5h, 2h, 3h, 4h, 5h, 6h, 7h, 8h, 9h, 10h, 11h, 12h  $\pm$ 5min, respectively. The distance between pain point and drug administration point (R1, R2) was measured and recorded, and the analgesic range diameter D = (R1 + R2).

**(2) Analgesic maintenance time, onset time and acupuncture pain intensity were measured (Test 2):** the intensity of acupuncture pain was measured before and after 15min, 1h, 4h, 8h, 10h, 12h, 14h, 18h, 21h, 24h, 27h, 30h, 33h, 36h, 48h, 72h;

**Baseline pain measurement:** Before drug administration, visual analogue scale (VAS) was used to measure the pain pressure baseline value (g) of VAS=4,5,6 in the pain test area, repeated for 3 times, and average value was taken respectively, namely the baseline value;

**Acupuncture pain intensity measurement:** a baseline value of VAS=4 was applied to the blank area to remind subjects of the sensation; In the pain test area, the baseline VAS=4 pressure was applied to the area, and the subjects were asked to compare the feeling with the blank area, and the feeling was "weaker", "similar", "stronger"?

When it was "weaker", baseline pressure at VAS= 5,6 was successively given and the inquiry process was repeated. When VAS=6 pressure was applied, subjects felt weaker and did not continue to increase the pressure. When it was "similar", record the maximum pressure value applied at this time; When it was stronger, the maximum pressure of the previous application was recorded and the onset time of analgesia maintenance time and the intensity of acupuncture pain were counted.

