**Data review meeting**

Before the database locked, the draft data management report and all data lists are collected, Bidders, researchers, data management and statistical analysts in the blind state under the joint audit data does not solve the problem, and according to the statistical analysis has been made to the clinical trial division and verification report serious adverse events and treatment records, such as data audit report after the meeting to be finalized data management and the crowd partition plan, etc.

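### The reason given for not blinding researchers covers only those who handle the drug; the separate pain assessor in cohort A is never masked, and the blinding provisions contradict each other

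*Protocol*

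**What the plan says.** The Study design section calls the trial "A randomized, single-blind, positive-controlled, single-dose subcutaneous, dose-increasing clinical study". The Blinded design section gives the reason for stopping at single-blind, "Because the packaging and properties of the test drug and the control drug in this study were different", and concludes that "it was impossible to blind the researchers". It makes no distinction between researchers who handle the drug and those who do not.

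The plan separates two roles. The trial 2 test method says "The drug administration investigator and the pain measurement investigator should not be the same person"; the note under Table 4 repeats it, "The drug administration researcher and the pain measurement researcher should not be the same person"; and the Blinded design section says so again. No section says that the person measuring pain is kept unaware of the group.

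Pain is read by stepped pressure. The assessor applies the pre-measured pressure to the blank area and then to the test area, and "the subjects were asked to compare the feeling with the blank area". The answer (weaker, similar or stronger) decides whether the next pressure is applied and which value is recorded (Pharmacodynamics methods).

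Three other provisions bear on blinding:

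- Drug numbers are coded by arm, "where T stands for experimental drug and Z stands for control drug", and the label also carries the drug name and manufacturer (Study preparation).
- Before database lock, data are reviewed by "Bidders, researchers, data management and statistical analysts in the blind state" (Data review meeting).
- Emergency letters are supplied so that an investigator can learn a subject's group (Blinded design).

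**The concern.** Different packaging and properties are visible to whoever prepares or injects the product. They are no reason why a second person, who does neither, must know the group. Separating injector and assessor protects against observer bias only if the assessor lacks the allocation. As written, the plan bears the burden of two people without securing that benefit, and its general statement classes the assessor as unblinded.

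The readings concerned are onset, duration and intensity of analgesia in cohort A, the only cohort with a control. The Observation indicators section sets these out for comparison between the two drugs, and the Pharmacodynamics analysis section estimates the difference between groups with a 95% confidence interval. An assessor who knows which subject received the long-acting product can influence how the pressure is applied, how the question is put and what is recorded.

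The text also cannot be followed consistently: researchers declared unblinded are said to review data blind, and investigators declared unblinded are given letters from which to learn the group.

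**Working it through.** **Size of the comparison.** Table 1 gives 6 test and 3 control subjects in cohort A. The batches described under Randomization agree: test 1 + 2 + 3 = 6, control 1 + 1 + 1 = 3, total 9, matching subject numbers 1001 to 1009. Cohorts B to E have no control.

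**Who could be masked, on the plan's own reason.**

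| Role | Sees the product by necessity? | Plan's provision |
|---|---|---|
| Subject | No | Blinded |
| Preparer, injector | Yes | Not blinded; the stated reason applies |
| Pain assessor | No; a different person from the injector | Not blinded; the stated reason does not apply |
| Skin-irritation scorer | Not stated; no rater named | Nothing stated |

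**Contradictions.** Blinded design: researchers are not blind. Data review meeting: researchers review in a blind state. Emergency letters: an investigator does not yet know the group. The first statement cannot hold for all researchers if either of the others applies to any of them.

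**How sensitive 6 v 3 is to observer bias.** The plan states no SD, effect size or power, so the bias is assumed, in SD units, with no true difference. A two-sample t-test stands in for the planned mixed model.

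- Standard error = SD × √(1/6 + 1/3) = 0.71 SD.
- Half-width of the 95% interval on 7 degrees of freedom = 1.67 SD.
- Shift 0.5 SD: noncentrality 0.5/0.71 = 0.71; two-sided false-positive rate about 9%.
- Shift 1.0 SD: noncentrality 1.0/0.71 = 1.41; two-sided false-positive rate about 23%.

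**Would the injection pattern reveal the group?** The inputs are strengths of 200 mg/10 mL (test) and 100 mg/10 mL (control) from Study design, and 1.2 mL per point from the trial 2 test method. No control volume is stated; 150 mg in both arms is an assumption.

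- Test: 150/20 = 7.5 mL; 7.5/1.2 = 6.25 points.
- Control: 150/10 = 15 mL; 15/1.2 = 12.5 points.
- If volumes were instead matched at 7.5 mL, the points would match and the control would receive 7.5 × 10 = 75 mg.

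On the first assumption, the assessor, who works on marked areas tied to the injection points, would see about twice as many points in a control subject.

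**The case against.** The trial is openly single-blind and says why. The subject, who is blinded, gives the verbal answer and compares it with their own blank area at pressures fixed before dosing. Analgesia is a secondary purpose. The plasma concentrations behind the pharmacokinetic results are measured by LC-MS/MS and are not exposed to assessor expectation. Requiring a separate assessor three times may have been meant as masking. All of this limits the consequence. It does not supply the missing provision, and the only general statement about researchers says the opposite.

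Full masking may not be achievable. At 150 mg in both arms the number of injection points differs about twofold, and the plan describes the test solvent as irritating, which could be a further cue. This stands: the bias can be reduced, but the documents do not show that it can be removed. The skin-irritation score, a main indicator, is rated directly by an observer, but no separate scorer is provided for, so masking that role may need staff the plan does not mention.

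Two stronger readings are tempting. A reader might infer that the T and Z prefixes unblind the data review. The documents do not show this: drug numbers belong to the packaging, subjects carry neutral four-digit numbers, and nothing says that the drug number enters the eCRF or the listings reviewed. A reader might also try to express the bias in hours, as a one-visit move of the control median. The visit lists disagree (18 h appears under Pharmacodynamics methods but not under Observation indicators). Moving one of three values also need not move the median, and expectation favouring the test drug would shorten control duration. No figure in hours is supported.

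**Conclusion.** The point holds in limited form. The stated impossibility covers only the preparer and injector. The pain assessor is already a separate person, and the plan neither masks that person nor says why it cannot. This leaves cohort A's pain readings open to observer influence on how they are elicited and recorded, in a 6 v 3 comparison. Its actual size is unknown; the 9% to 23% range rests wholly on an assumed shift of 0.5 to 1.0 SD and a simple t-test. The conflict between the Blinded design section, the Data review meeting section and the emergency letters is textual and needs no assumption. The change is worth making because it is cheap and concerns the only randomised comparison; the primary pharmacokinetic results do not depend on it.

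**What to change.** 1. **Blinded design.** Confine the impossibility statement to staff who prepare or inject the drug. Require that the cohort A pain assessor does not see the allocation list, product, label or injection until cohort A data are locked. Apply the same rule to the skin-irritation scorer where existing staffing allows; otherwise say that this score is unmasked.
2. **Limits of masking.** State the control volume and number of injection points in cohort A. If they differ between arms, acknowledge that assessor masking may be partial.
3. **Drug numbers and labels (precaution).** For cohort A, use numbers without the T or Z code, with the key held by the randomisation statistician, and cover the product name in front of subject and assessor. Anyone who sees the present number learns the arm.
4. **Data review meeting and emergency letters.** State who is blind at the review, or delete the claim that it is blind, and say which investigators the letters are for.

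The cost is wording, a relabelling step for nine subjects, and keeping the pain assessor away from the injection. The sample size is unchanged and no extra pain assessor is needed. Masking the skin scorer may need one further person.

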**Table 1: Dose escalation protocol for single dose trials in healthy subjects**

| array | Dose (mg) | Number of healthy subjects (n)    |                                     |
|-------|-----------|-----------------------------------|-------------------------------------|
|       |           | Experimental group                | Control group                       |
|       |           | long-acting ropivacaine injection | ropivacaine hydrochloride injection |
| A     | 150       | 6                                 | 3                                   |
| B     | 230       | 8                                 | --                                  |
| C     | 300       | 8                                 | --                                  |
| D     | 350       | 8                                 | --                                  |
| E     | 400       | 8                                 | --                                  |
| Total |           | 38                                | 3                                   |

Positive control was set for cohort A, and no positive control was set for other dose groups. The study began at the minimum dose, with each subject receiving only one dose and only one dose cohort at a time. Safety assessments were conducted on days 7 and 21 after dosing, and the next cohort/batch trial was determined based on the results. If no significant adverse effects were observed in the maximum dose cohort (400mg), dose-escalation was not continued.

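### Cohort A's randomisation list is specified in 1:1 blocks, which contradicts the planned 6:3 split and its 2+1 and 3+1 batches

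*Protocol*

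**What the plan says.** **Planned numbers.** Table 1 gives cohort A 6 test and 3 control subjects. The text below it adds: "Positive control was set for cohort A, and no positive control was set for other dose groups". The text under Table 4 (Randomization) runs the cohort in three batches. The first has one test and one control subject, and the second has two test and one control. For the last batch it says: "In the third group, there were 3 cases in experimental group and 1 case in positive control group". It also says that the SAS allocation table for subjects 1001 to 1009 is produced batch by batch.

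**List specification.** The Blind storage paragraph of Blinded design covers the same cohort and the same SAS table, and describes the table as one "which randomly generated by statistical units using SAS(9.4 or higher version) in 1:1 block groups". On block size it says: "The selected block length and random seed number are sealed in the blind as confidential data".

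**Code break.** The paragraph on opening emergency letters says: "Once the emergency mail is opened, the subject with this number will withdraw from the study".

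**The concern.** Two sections give the randomisation statistician different instructions for the same nine subjects. A list built from Blinded design would in most cases change how many cohort A subjects receive each product, and would not follow the planned build-up of 1, 2 and then 3 test subjects per batch. Cohort A is the only place where test and control are compared under randomisation, and its safety review informs the decision to go on to the next cohort.

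The code-break rule is a separate and smaller matter. Each subject is dosed once, so leaving the study after dosing cannot reduce exposure. Read literally, the rule would only end the remaining scheduled observations.

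**Working it through.** **Inputs.** Cohort A has n = 9 with a 6:3 split (Table 1). The batches are 1+1, 2+1 and 3+1, numbered 1001 to 1009 (Table 4 and its text). The list is in 1:1 blocks (Blinded design). The block length is sealed, so even lengths from 2 to 18 are tried as an assumption.

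**Step 1: reproduce the plan's figure.** Test: 1 + 2 + 3 = 6. Control: 1 + 1 + 1 = 3. Total: 9 = 1009 − 1001 + 1. For study 2 as a whole, 6 + 4 × 8 = 38 test and 3 control, or 41, as in Table 1 and under Number of planned subjects. The 6:3 plan is consistent throughout, and 1:1 is the exception.

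**Step 2: one continuous 1:1 list over nine subjects.** Nine is odd, so complete 1:1 blocks cannot fill the cohort and the last block must be cut short. Let B be the block length, h = B/2, f the number of full blocks and r = 9 − fB the subjects left over. Then

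P(test = fh + k) = C(h, k) × C(h, r − k) / C(B, r).

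| B | Calculation for 6:3 | Possible test:control splits | P(6:3) |
|---|---|---|---|
| 2, 4, 8 | 8 subjects split 4:4, one left over | 5:4 or 4:5 | 0 |
| 10 | 9 drawn from 5 + 5 | 5:4 or 4:5 | 0 |
| 6 | C(3,3)C(3,0)/C(6,3) = 1/20 | 3:6, 4:5, 5:4, 6:3 | 0.05 |
| 12 | C(6,6)C(6,3)/C(12,9) = 20/220 | 3:6, 4:5, 5:4, 6:3 | 0.091 |
| 18 | C(9,6)C(9,3)/C(18,9) = 7056/48620 | 0:9 to 9:0 | 0.145 |

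For B = 6 the full distribution is 3:6 with probability 0.05, 4:5 with 0.45, 5:4 with 0.45 and 6:3 with 0.05.

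A general bound needs no block length. A 1:1 list treats the two products symmetrically, so P(6:3) = P(3:6). The two cannot both occur, so P(6:3) is at most 0.5, and no choice of 1:1 block lengths makes it certain.

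**Step 3: the exact batch pattern from that list.** It has probability 0 for lengths 2, 4, 8 and 10. For length 6, 6 of the 400 pairs of blocks give the pattern, or 0.015. For length 12 it is 24/924 = 0.026.

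**Step 4: 1:1 blocks started afresh in each batch.**

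| Batch | B = 2 | B = 4 | B = 6 | B = 8 |
|---|---|---|---|---|
| 1+1 | 1 | 0.67 | 0.60 | 0.57 |
| 2+1 | 0.50 | 0.50 | 0.45 | 0.43 |
| 3+1 | 0 | 0 | 0.20 | 0.23 |

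For example, 3+1 with B = 6 is C(3,3)C(3,1)/C(6,4) = 3/15 = 0.20. A block of 2 delivers the first batch exactly. At none of these lengths are the other two assured.

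**Step 5: one list per batch at the batch's own ratio.** One control is placed at random in each batch. This gives 2 × 3 × 4 = 24 possible lists, every one of them 6:3.

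**Step 6: the code-break rule against the follow-up rules.** Adverse event collection time records events to 21 days after dosing. The Adverse events part of the statistical section assesses every dosed subject over the same period and follows events until normal or stable. Note 21 to Table 10 asks for a withdrawal visit. Safety follow-up is therefore kept. Concentration samples (Table 2) and pain readings run to 72 h, and nothing similar protects those still due after withdrawal. One control withdrawn is 1/3 of that arm.

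**The case against.** The best defence is that the Randomization text already gives the counts batch by batch and agrees with Table 1, so a careful statistician would follow it and treat 1:1 as a slip. That is the likely outcome, and it shows which passage to correct. It does not excuse leaving an incompatible rule in the section that specifies the list.

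A reader might infer more than the protocol supports:

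- That 1:1 blocks can never give 6:3. This is exact for complete blocks and for lengths 2, 4, 8 and 10. Cut-short blocks of 6, 12 or 18 can reach it by chance.
- That all three batches conflict with the rule. The first batch is itself 1:1.
- That cohort A would have 4 or 5 test subjects. This holds for lengths 2, 4, 8 and 10. For length 6 the range is 3 to 6.
- That the code-break rule ends safety follow-up or discards data. Follow-up is required elsewhere, as shown in the working. The definitions under Analysis of the crowd keep every dosed subject in the Safety Set, and keep concentrations already obtained. Only later scheduled concentration and pain data are at risk, and only if a letter is opened.

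**Conclusion.** The list specification is wrong as written and should be corrected before any list is generated from it. Its size depends on the sealed block length: the planned 6:3 has probability 0 for lengths 2, 4, 8 and 10, 0.05 for length 6, and no more than 0.145 among the lengths tried. This assumes a single continuous list with its last block cut short. Restarting 1:1 blocks in each batch does not rescue the plan either.

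The code-break rule is secondary. It needs reconciling with the follow-up passages, and its effect is limited to scheduled data due after a letter is opened.

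Because the section also says "it was impossible to blind the researchers", a reader might infer an error in the masking of the pain assessor. The documents do not show one. The study is declared single-blind, the person who injects and the person who measures pain must differ, and no passage gives the latter the list. The assessor also sees the injection sites, whose number may differ between a 20 mg/mL and a 10 mg/mL product, so withholding the list might not mask the assessor anyway.

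**What to change.** In Blinded design, Blind storage, replace the 1:1 block wording with one permuted list per batch: two subjects at 1:1, three at 2:1 and four at 3:1. Refer to the batch counts under Table 4 so that the two sections cannot diverge again. This always yields 6:3 and changes neither the sample size nor the conduct of the batches.

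In the paragraph on opening emergency letters, state that opening a letter does not by itself end scheduled data collection for a subject who still consents, and that pain readings taken afterwards are flagged as unblinded. Align this with Adverse event collection time and the Adverse events part of the statistical section.

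The cost is one sentence for each change, with no extra subjects, visits or staff. If a list has already been generated, check it against the three batch counts and record the result.
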